## Methods

### Study design

This protocol was developed for an assessor-blinded superiority randomized controlled trial. The eligible participants are recruited 1–3 days after surgery at the orthopedic ward of Seoul National University Bundang Hospital (Seongnam-si, Gyeonggi-do, Korea). The participants are then randomized based on 1:1 allocation to two groups: the digital group will undergo a rehabilitation program using a digital healthcare system, whereas the conventional group will undergo a conventional rehabilitation program. Patients will be discharged home a few days after the surgery with a shoulder brace on the affected shoulder and will immediately begin the rehabilitation program, including early mobilization of the shoulder girdle. Until post-op 6 weeks, when they will remove their braces, both groups will use brochures received at the time of discharge that provide instructions on mobilizing the affected shoulder girdle. From post-op 6 to 12 weeks, participants in the digital group will perform exercises using an AR-based digital healthcare system (UINCARE Home+; UINCARE Corp., Seoul, Korea), whereas participants in the conventional group will perform exercises using only the brochures provided by the hospital. Participants in both groups will be allowed hospital visits for exercise education by physical therapists, up to three sessions (30 min per session) over 12 weeks. The primary and secondary outcomes will be measured at baseline and at post-op 6, 12, and 24 weeks. An overview of the study design and process is given in Fig. 1.

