### Randomization and blinding

Participants will be randomized after the baseline evaluation and allocated to either the Digital or conventional group at a 1:1 ratio. Randomization sequences will be computer-generated blocks, without stratification, by the institution’s biostatistician, who is independent of the study team. The randomized allocation information was sealed in a numbered opaque envelope. The envelope seals will be checked monthly by the principle investigator to make sure the future participants’ allocation is kept blinded. Participant allocation and follow-up arrangements will be managed by the study coordinator, who will not be blinded to the participants’ group assignments. Assessments will be performed by two research therapists from the study team, who will be blinded to the participants’ intervention groups.

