### Primary hypothesis and data analysis

The primary hypothesis is that participants in the rehabilitation program using a digital healthcare system will demonstrate better shoulder function compared to those in the conventional rehabilitation group. Analyses will be performed using both intention-to-treat and per-protocol approach. The primary outcome measure for this study will be SST scores at post-op 12 weeks. A two-way repeated-measures ANOVA will be used to explore the effects of intervention, time, and intervention by time interaction on SST scores. The results will be presented with a mean difference with 95% confidence interval at each follow-up time point. Continuous secondary outcomes will be analyzed using repeated-measures ANOVA at each post-op 12 weeks and 24 weeks. Subgroup analysis based on the size of the tear will be performed only if there are sufficient participants in all four subgroups (small, <1 cm; medium, 1–3 cm; large, 3–5 cm; massive, ≥5 cm tear or more than two tendons involved) [23]. Statistical analysis will be performed after the 24-week follow-up measurement of the last enrolled participant is done and no inter-rim analysis will be performed during the trial. All tests will use a 5% level of significance (*P* < 0.05).

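### The planned test for continuous secondary outcomes is undefined as to visits and model term, and leaves the collected baseline unused as a covariate

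*Protocol article*

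**What the plan says.** The analysis of continuous secondary outcomes is one sentence in the protocol article, Primary hypothesis and data analysis: "Continuous secondary outcomes will be analyzed using repeated-measures ANOVA at each post-op 12 weeks and 24 weeks".

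The sentences just before it deal with the primary outcome: "A two-way repeated-measures ANOVA will be used to explore the effects of intervention, time, and intervention by time interaction on SST scores", and then "The results will be presented with a mean difference with 95% confidence interval at each follow-up time point".

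On timing, Study design states "The primary and secondary outcomes will be measured at baseline and at post-op 6, 12, and 24 weeks", and Table 3 marks every secondary outcome at all four times. Study design also states "The eligible participants are recruited 1–3 days after surgery", and Randomization and blinding adds "Participants will be randomized after the baseline evaluation". Baseline is therefore an early post-surgical value, taken before allocation.

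Under Intervention, both groups follow the same brochure programme until week 6, and the digital system is used only from week 6 to week 12.

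**The concern.** A repeated-measures ANOVA compares two or more occasions within patients, so it cannot be run at 12 weeks alone or at 24 weeks alone. To run it, the analyst must choose the visits in the model and the term that counts as the test. The sentence settles neither.

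The choice matters in this design for two reasons. First, the arms are treated alike until week 6, so a term that averages over baseline or week 6 mixes in visits where no treatment difference is expected. Second, baseline is measured within days of surgery and may say little about status at 12 or 24 weeks. If so, subtracting it adds noise, whereas using it as a covariate does not.

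At stake are the width of the confidence intervals for the secondary outcomes, and whether the reported test answers the question of a difference at 12 and at 24 weeks.

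**Working it through.** **Inputs from the protocol article (Sample size).** SST difference 2.15, SD 3.7, two-sided 5%, 80% power, 49 per group, 15% attrition, 115 in total. These are for SST only; no such figures are given for the secondary outcomes.

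**Assumptions.** The SST figures stand in for a secondary outcome. The correlation r between baseline and follow-up is not given, so a range of 0.1 to 0.3 is taken, with 0.5 for comparison. Week 6, where used, has the same correlation with the other visits. SDs are equal at all visits, except in step 6. The effect is present at the follow-up visit and absent at baseline and week 6.

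**Step 1: the plan's own figure.** The standardized difference is 2.15/3.7 = 0.58. A two-sample t-test with 80% power needs 47.5, so 48 per group, against 49 stated. 98/0.85 = 115.3, against 115 stated. The plan's figure reproduces to within rounding and is not in question. Power with 49 per group is 81%.

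**Step 2: baseline plus one visit, interaction term.** With two occasions the group-by-time F equals the squared t on change from baseline. In a simulated data set both were 11.958. The variance of change is 2(1−r)s².

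**Step 3: baseline plus one visit, group main effect.** This tests the mean of the two visits. The effect is halved and the variance is s²(1+r)/2.

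**Step 4: baseline, 6 and 12 weeks.** The interaction is a two-degree-of-freedom test and is not the change test: in a second simulated data set its F was 8.10, against 7.28 for the squared t on change. The group main effect is cut to a third, with variance s²(1+2r)/3.

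**Step 5: single-visit comparisons.** The follow-up score alone has variance s². ANCOVA has variance (1−r²)s².

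Power with 49 per group:

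| Reading | r = 0.1 | r = 0.3 | r = 0.5 |
|---|---|---|---|
| Two-visit interaction (change) | 57% | 67% | 81% |
| Two-visit group main effect | 48% | 42% | 38% |
| Three-visit interaction | 59% | 70% | 85% |
| Three-visit group main effect | 32% | 26% | 21% |
| Follow-up score alone | 81% | 81% | 81% |
| ANCOVA at the visit | 82% | 85% | 91% |

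The efficiency of change relative to ANCOVA is (1−r²)/[2(1−r)] = (1+r)/2. At r = 0.1 this is 0.55, so 1/0.55 = 1.82 times the patients; at r = 0.3 it is 0.65, so 1/0.65 = 1.54 times. Below r = 0.5, change is also less precise than ignoring baseline.

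**Step 6: unequal SDs.** Patients a few days after surgery may be uniformly limited, which would compress the baseline SD. With baseline SD equal to k times the follow-up SD, the variance of change is (1 + k² − 2rk)s². At k = 0.5:

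- r = 0.1: 1.15/0.99 = 1.16, so 16% more patients than ANCOVA.
- r = 0.3: 0.95/0.91 = 1.04, so 4% more.

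The cost of change scores therefore depends heavily on two quantities that the documents do not give.

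**The case against.** A reader might infer that the sentence can only mean a change-from-baseline test. The documents do not support that. Models with all visits up to 12 or 24 weeks, a model with 12 and 24 weeks as the two occasions, and per-visit contrasts from one model can all be run. The preceding sentence, "The results will be presented with a mean difference with 95% confidence interval at each follow-up time point", even points towards a difference at follow-up, although it follows the SST sentence and may not extend to the secondary outcomes. If per-visit differences are meant, the gain from ANCOVA over the follow-up score alone is only about 1 to 4 power points at r = 0.1 to 0.3.

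A reader might also take 54–82% more patients as the cost of the plan. That figure needs the change-score reading, the assumed r and equal SDs together, and step 6 shows how far it falls when the SDs differ.

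It is also fair to say that the treatment comparisons are unbiased under randomization, and that a condensed article may leave covariates to an analysis plan that is not shown. The absence of a covariate would not be a point by itself. What stands is that the article does fix a method, and the method as worded does not identify a test.

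**Conclusion.** The concern holds as one of definition and precision. The sentence names neither the visits nor the term tested, and the method it states does not use the baseline as a covariate. No reading is biased, and the sample size for SST is unaffected. Group main effects that include baseline or week 6 dilute the effect because of the design itself. The two-visit interaction is exactly a change-score test. Per-visit contrasts are sound but leave the precision available from baseline unused.

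The spread of power in the table is illustrative only. It rests on SST planning figures, assumed correlations and assumed equal SDs, and the actual loss for any secondary outcome cannot be computed from the documents. The direction is firmer: with baseline as covariate the analysis is never less precise than change scores, nor, apart from one degree of freedom, than follow-up scores alone.

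**What to change.** Replace the sentence on continuous secondary outcomes with:

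> For each continuous secondary outcome, the between-group adjusted mean difference with 95% CI at 12 weeks and at 24 weeks will be estimated from a mixed model for repeated measures (or ANCOVA at each visit) with the baseline value as covariate.

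One of the two models should be chosen, and the choice recorded before the data are analysed. The cost is wording in the protocol or analysis plan. No further patients, visits or measurements are needed, because Table 3 already schedules every secondary outcome at baseline.

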**Other measures**				
Demographic information	X			
Medical History	X			
Rotator cuff tear size	X			
User satisfaction questionnaires^a^			X	X

*NRS* numeric rating scale, *ROM* range of motion, *MMT* manual motor test, *DASH* disabilities of the arm, shoulder and hand, *SPADI* shoulder pain and disability index, *EQ-5D-5L* European Quality of Life Index

^a^Digital group only

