### Sample size

A minimal clinically important difference (MCID) in scores on the SST in patients with rotator cuff tear was reported to be 4.3 [21], and the average score on the SST at post-op 3 months in a previous study was 6.34 (SD = 3.7) [22]. The minimum sample size for the present study was calculated *t*-test based on a 2.15-point difference in SST score (50% of the MCID) and an SD of 3.7, while allowing a 5% probability of two-sided type 1 error and applying 80% statistical power. Forty-nine subjects will be required in each group to allow 15% attrition per group; thus, a total of 115 subjects will be required for the study.

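### Tear size is collected at baseline but left out of the stated primary model, and its only stated use is a four-category subgroup analysis with an unquantified, all-or-nothing trigger (minor)

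*Protocol article*

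**What the plan says.** All references are to the protocol article.

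- **Collection.** Table 3 lists "Rotator cuff tear size" among the other measures, marked at the baseline visit only.
- **Randomization and blinding.** "Randomization sequences will be computer-generated blocks, without stratification". Allocation follows the baseline evaluation, which itself follows surgery.
- **Primary hypothesis and data analysis.** The SST model is a two-way repeated-measures ANOVA with terms for intervention, time and their interaction. No baseline covariate is named.
- **Subgroups (same section).** "Subgroup analysis based on the size of the tear will be performed only if there are sufficient participants in all four subgroups". The four categories are small, medium, large and massive, the last defined by size or by the number of tendons involved. No count is given, nor whether it applies per category or per category and arm. Nothing is said about what happens if one category falls short.
- **Timing and level (same section).** All analysis takes place after the last participant's 24-week visit, and every test uses the 5% level.
- **Sample size.** The calculation is "based on a 2.15-point difference in SST score (50% of the MCID) and an SD of 3.7", with 49 per group and 115 in total.

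**The concern.** Two features of the stated methods are weak.

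First, a baseline variable that the plan thinks worth a subgroup analysis is absent from the primary model. If it predicts 12-week SST, that information is not used.

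Second, the subgroup rule is a pre-specified condition without a number. It depends on baseline counts rather than on outcomes, which limits the harm. But as written, whether the counts suffice can be decided when all outcomes are already in hand, so whether the analysis is run and reported remains a matter of choice. The rule is also all-or-nothing: one thin category removes the analysis for the other three.

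What is at stake is some precision in the primary estimate, and whether the trial can say anything usable about tear size. The validity of the primary comparison is not at stake.

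**Working it through.** **Inputs from the Sample size section:** SD 3.7, difference 2.15 SST points, two-sided alpha 0.05, power 80%, 49 per group, 15% attrition. **Not in the document, so assumed:** the share of SST variance explained by tear size (R², 5–15%) and the tear-size distribution.

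**1. The plan's own figure.** With the normal approximation, n = 2 × [(1.960 + 0.842) × 3.7 / 2.15]² = 46.5, so 47 per group. The noncentral t gives 48 (power 80.4%); at 49 the power is 81.3%. Attrition: 98 / 0.85 = 115.3, against the stated 115. The sample size reproduces, and this point does not touch it.

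**2. Gain from adjustment.** Residual SD = 3.7 × √(1 − R²), with power from the noncentral t at 49 per arm.

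| Assumed R² | Residual SD | Power for 2.15 |
|---|---|---|
| 0 | 3.70 | 81% |
| 5% | 3.61 | 83% |
| 10% | 3.51 | 85% |
| 15% | 3.41 | 87% |

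**3. Precision within a category.** SE = 3.7 × √(2/n), and half-width = t(0.975; 2n − 2) × SE. In the best case, four equal categories, n = 98 / 8 = 12.25 per arm.
- SE = 3.7 × √(2/12.25) = 1.495.
- Half-width = 2.071 × 1.495 = 3.1 points.
- Power for 2.15 points = 28%.
- Difference detectable with 80% power = 4.4 points, about twice the design difference and just above the cited MCID of 4.3.

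If the rarest category has only 5 or 6 per arm (assumption), the half-width is 5.4 or 4.8 points on a 0–12 scale, and power is 13% or 15%.

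For 80% power at 2.15 points in every category, 4 × 2 × 48 = 384 evaluable patients would be needed. The plan has 98.

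**4. Can the trigger be met?** Chance that all four categories reach a minimum total count (both arms together) among 98 patients, by multinomial simulation under assumed shares:

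| Assumed shares (%) | at least 5 | at least 10 | at least 20 |
|---|---|---|---|
| 25/25/25/25 | 100% | 100% | 55% |
| 15/45/25/15 | 99.9% | 87% | 0.2% |
| 10/50/25/15 | 97% | 48% | 0% |
| 5/50/30/15 | 55% | 2% | 0% |

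The answer runs from near certainty to near zero, depending on two quantities that the document does not give.

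**5. How much an imbalance would move the estimate.** Take an assumed 40% with large or massive tears and treat tear size as two classes. The class difference implied by R² is 3.7 × √(R² / (0.4 × 0.6)), which is 1.7 points at 5% and 2.9 points at 15%. A 10-percentage-point imbalance between arms then shifts the unadjusted estimate by 0.1 × 1.7 = 0.17 to 0.1 × 2.9 = 0.29 points, against a target of 2.15.

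**6. What an interaction can show.** The difference in effect between two equal categories has SE = 3.7 × √(4/12.25) = 2.11. Power to detect a 2.15-point difference in effect is 17%, and 6.0 points is detectable with 80% power. The interaction asks the right question but is exploratory at this size.

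**The case against.** The strongest case against is this. The source is a condensed article; covariates, minimum subgroup counts and the form of the subgroup test may be set in an analysis plan that is not shown. Unstratified blocked 1:1 randomization is a valid design, the unadjusted standard error already allows for chance imbalance, and step 5 shows that a typical imbalance would matter little. A condition on baseline counts is also a caution against analysing very small groups.

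Most of that stands, and it limits the point. What survives is that the article does not merely stay silent: it states a specific model without the covariate, and it states a rule that cannot be applied without a number.

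Three stronger readings are tempting and not supported:

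- *That the lack of stratification or adjustment is an error or biases the result.* It does not; adjustment only adds precision.
- *That this sample can hardly meet the trigger.* That is true if the trigger means adequate power in each category. It is not true for a low minimum count: at least 10 in every category is reached 87% of the time with assumed shares of 15/45/25/15%.
- *That the plan treats tear size as an effect modifier and will test the categories separately.* The article never calls it an effect modifier or a prognostic factor, and it does not say whether the subgroup analysis means separate tests or an interaction.

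**Conclusion.** The point holds as a minor one. The primary comparison is valid as planned. Leaving tear size out of the model forgoes perhaps 2 to 6 percentage points of power (81% to 83–87%), on an assumed R² of 5–15% that the document neither supports nor contradicts.

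The subgroup rule is poorly fixed whatever the tear-size distribution. If one category is thin, nothing is reported. If all four are judged large enough, each estimate carries a half-width of about 3.1 points at best and about 5 points in a category with 5–6 per arm. Those within-category figures rest only on the plan's own SD and sample size plus the category split. The chance of meeting the trigger cannot be stated, and no conclusion here depends on it.

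**What to change.** Make both changes in writing before unblinding.

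1. Pre-specify tear size as a baseline covariate in the primary SST model.
2. Replace the all-or-nothing trigger with one pre-specified treatment by tear-size interaction, reported with its 95% CI and labelled exploratory. Show category estimates descriptively, without separate significance tests. State a minimum count per category and arm, and which neighbouring categories are merged when it is not reached.

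The cost is wording only; tear size is already collected. The statistical price is one degree of freedom for an ordered score, or a few for categories. An ordered score also assumes a linear trend. That is imperfect here, because the massive category also takes in tears involving more than two tendons and so is not purely a step in size. The interaction estimate will be imprecise (step 6) and should be described as such.

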### Participant safety and withdrawal

The potential risks for participants in this study are minimal. There is no independent oversight committee and adverse events (AEs) will be monitored by the research team at the scheduled follow-ups. Possible AEs include increased pain due to exercise and re-tear of the repaired rotator cuff tendons. Pain will be managed at the orthopedic outpatient clinic with pain medications or steroid injections, if needed. Surveillance of re-tear of repaired tendon will be routinely performed in post-op 12 weeks; however, if the re-tear is clinically suspected at any time during the follow-up periods, appropriate examinations and treatments will be provided. Participants in both groups can report AEs to the research team via direct telephone contact. Participants in the digital group will also receive a telephone number of the manufacturer for technical support.

Participants are allowed to leave the trial at any time. Participants can withdraw from the trial by informing the research team. Participants will be encouraged to visit the pre-scheduled follow-ups even if they withdraw from the study for data collection. Participants in both groups will be regularly reminded with phone calls and text messages to minimize loss of follow-ups and maximize the adherence to the trial.

## Discussion

The prevalence of rotator cuff tears is increasing as the general population ages, which will eventually lead to an increased incidence of rotator cuff repair surgery. Because post-op rehabilitation is a crucial element in restoring function and reducing pain after rotator cuff repair [24], the need for an effective method of post-op rehabilitation is emerging. Post-op rehabilitation of musculoskeletal disorders using VR and AR systems is at an early stage, with only a few published studies showing its feasibility [14, 15, 25, 26].

In this trial, a digital healthcare system will be implemented only during the off-brace (post-op 6–9 weeks) and active mobilization (post-op 9–12 weeks) phases. It will not be applied during the on-brace phase (immediate post-op period to 6 weeks) because exercise programs in this phase are mainly focused on low-intensity whole-body movements under support by a post-operative brace. Also from the previous literatures, patients at this phase have good compliance with seldom having difficulty following the exercise program [27, 28]. The cost of the digital healthcare system (170 USD per week) was also considered. To maximize the cost-effectiveness of rehabilitation using the digital system, we decided that it would only be applied during the off-brace and the active mobilization phases.

This trial would have several strengths. First, to our knowledge, this would be the first randomized controlled trial to compare the effectiveness of post-op rehabilitation using a digital healthcare system with that of conventional rehabilitation in patients who had undergone rotator cuff repair. Second, this trial will implement an AR-based digital healthcare system dedicated to post-op rehabilitation. Some previous studies have used commercial fitness programs such as the Nintendo Wii Fit^TM^ [14, 15], which comprises fitness programs for the general population. However, in this trial, the digital healthcare system is tailor-made for patients who have undergone rotator cuff repair surgery and provides specific exercise programs according to the patient’s rehabilitation phase and daily progress. With this rehabilitation-oriented program, we anticipate that the effectiveness of AR-based post-op rehabilitation will be amplified.

In conclusion, this study will examine the effectiveness of an AR-based digital healthcare system for post-op rehabilitation in the patients after rotator cuff repair. The study will add evidence for the application of digital healthcare systems in post-op rehabilitation.

